#### Exploratory biological endpoints

The trial will collect biological samples to investigate mechanistic effects of TRE. BM and blood specimens at baseline and end of treatment will be analysed for changes in MM cell biology and metabolism. These include examining clonal evolution and gene expression in MM cells, shifts in immune cell profile in marrow, and levels of metabolic hormones. Serum and plasma will be used for exploratory metabolomic and proteomic analyses to generate hypotheses on the biological impact of TRE. The microbiome has been linked to cancer pathologies and treatment [22]. It largely contributes to immune system maturation [31] and diet is a main driver of both microbiome composition and function [29]. Thus, TRE-induced microbiome changes could contribute to treatment outcome. Microbiome composition will be monitored using metagenomic sequencing.

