## Statistical methods

All analyses will follow the ITT principle. A per-protocol (PP) analysis will be performed as a sensitivity analysis. Safety analyses will include all patients who started the intervention or control and may be stratified by actual fasting behaviour if crossovers occur.

For the primary endpoint feasibility, the adherence rate in arm A will be calculated as patients with ≥ 80% fasting-day compliance divided by total patients in arm A, with a 95% CI (Clopper-Pearson). No hypothesis test is needed for this single-arm feasibility measure, and we will compare the observed adherence to our target threshold.

For the preliminary efficacy endpoint of CR with MRD negativity at T_1_, proportions between both arms will be compared using a chi-square or Fisher’s exact test to explore differences. We will estimate the absolute difference in CR/MRD rates between arm A and B with CI. To adjust for potential imbalances and our stratification factors, we will perform logistic regression: The dependent variable will be CR/MRD-negative status, and independent variables will include treatment arm, line of therapy, baseline BMI category, and gender. The logistic regression will provide an adjusted OR with a 95% CI for achieving CR/MRD negativity, yielding a hypothesis-generating effect size. We will examine MRD negativity alone and CR (regardless of MRD) separately as post hoc analyses.

Secondary endpoint analysis will be descriptive and exploratory: Response categories (VGPR, PR, SD) will be tabulated by arm. Survival endpoints (PFS, OS) will be plotted using Kaplan–Meier curves. Continuous measures like weight, BMI, and lab values will be analysed using mixed-effects models or paired t-tests within arms and compared between arms by analysis of covariance (ANCOVA), adjusting for baseline. AEs will be summarised by category and grade. QoL and fatigue scores will be analysed by calculating changes from baseline to T_1_. Mean changes will be compared between arms using t-tests or non-parametric tests if data are not normally distributed. Exploratory biological endpoints will be analysed for hypothesis-generation.

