We anticipate minimal missing data for primary endpoints since adherence can be assessed if diary data are > 80% complete. Participants who discontinue TRE or withdraw before adherence can be evaluated will be counted as non-adherent for the feasibility endpoint, and intervention pauses and reasons will be summarised descriptively. If a patient lacks MRD status at T_1_, they will be considered not achieving CR/MRD. Missing data in secondary patient-reported outcomes will be handled by analysing available cases or using imputation methods. For survival, standard censoring at last follow-up is done for those without events. A sensitivity analysis using multiple imputation for missing outcome data will be explored to ensure robustness.

All statistical tests will be two-sided, with *p*-value < 0.05 considered significant for exploratory, hypothesis-generating purposes. No adjustments for multiple comparisons are planned, given the exploratory nature.

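### The blanket no-adjustment rule at p < 0.05 also covers, as worded, the omics and microbiome analyses, where a false discovery rate rule would serve better (minor)

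*Protocol article*

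**What the plan says.** All of this is in the protocol article.

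- **Statistical methods, closing paragraph.** The rule opens with "All statistical tests will be two-sided" and sets the threshold as "0.05 considered significant for exploratory, hypothesis-generating purposes". It ends: "No adjustments for multiple comparisons are planned, given the exploratory nature". No class of endpoint is excepted.
- **Exploratory biological endpoints.** For marrow and blood specimens: "These include examining clonal evolution and gene expression in MM cells, shifts in immune cell profile in marrow, and levels of metabolic hormones". Further: "Serum and plasma will be used for exploratory metabolomic and proteomic analyses to generate hypotheses on the biological impact of TRE". And: "Microbiome composition will be monitored using metagenomic sequencing". No number of features is given for any platform.
- **Statistical methods, secondary and exploratory analyses.** Tests or models are named for weight, laboratory values, quality of life and fatigue. For the biological work the only statement is: "Exploratory biological endpoints will be analysed for hypothesis-generation".
- **Discussion.** The biomarker analyses are said to need validation before they are relied on, and the stored samples are described as a possible source of new research questions.

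**The concern.** Declaring no adjustment is acceptable for a short list of clinical and patient-reported outcomes in a feasibility trial, because each result can be read on its own with its estimate and interval. A high-dimensional platform differs in that its output is a selected list. Generating hypotheses there means choosing which metabolites, proteins, transcripts or taxa to follow up, so the useful property of the list is the share of it that is noise. An unadjusted 0.05 cut-off leaves that share uncontrolled and unreported.

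The article does not leave the matter open for a later document. It says that no adjustment is planned, for all tests. A later analysis plan or laboratory plan that used false discovery rate control would depart from the published sentence. At stake is the value of the exploratory list for choosing what to validate. The feasibility conclusions are not affected.

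**Working it through.** **Inputs from the article.** Two-sided threshold 0.05, no adjustment (Statistical methods). 54 patients randomised 1:1 (Trial design), so 54/2 = 27 per arm. Retention criterion 85% (Progression criteria).

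**Inputs that are assumptions.** Number of features m, share truly changed π, standardised effect d, independent features, and one two-sample t-test per feature. The article gives none of these.

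**The plan's own figure.** The article states no false-positive figure to reproduce. Its one computed design figure, a margin of about ±15 points for adherence, does reproduce: 1.96 × √(0.80 × 0.20 / 27) = 0.151. This confirms 27 per arm as the basis.

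**Step 1: no true effect.** Expected hits = 0.05 × m. That gives 5 for m = 100, 50 for m = 1,000 and 250 for m = 5,000. Correlation between features leaves these expectations unchanged, though it makes the count more variable.

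**Step 2: false share of the hits.** Expected share = 0.05(1 − π) / [0.05(1 − π) + power × π]. With 27 per arm, power per feature is 0.438 at d = 0.5 and 0.822 at d = 0.8. Example, π = 5% and d = 0.5: 0.0475 / (0.0475 + 0.0219) = 68%.

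| Truly changed (π) | False share, d = 0.5 | False share, d = 0.8 |
|---|---|---|
| 1% | 92% | 86% |
| 5% | 68% | 54% |
| 10% | 51% | 35% |
| 20% | 31% | 20% |

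**Step 3: where the share passes one half.** Setting the formula to 0.5 gives π = 0.05 / (0.05 + power). For d = 0.8 this is 0.05 / 0.872 = 5.7%; for d = 0.5 it is 0.05 / 0.488 = 10.2%. At 85% retention (0.85 × 27 ≈ 23 per arm) the limits rise to about 6.2% and 11.6%.

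**Step 4: effect of a false discovery rate rule.** Simulation with m = 1,000, 27 per arm, Benjamini-Hochberg at 10%:

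| Scenario | Unadjusted hits (false) | Benjamini-Hochberg 10% |
|---|---|---|
| No true effect | about 50 (all) | about 0.1 |
| 5% changed, 0.8 SD | about 89 (48) | about 22, of which 2 false |
| 5% changed, 0.5 SD | about 69 (47) | about 2 in total, against 50 truly changed features; none at all in more than a third of runs |

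**The case against.** The strongest reply is that the article never says features will be screened one at a time. It names no feature-level test for any platform, and such data can be analysed by ordination, diversity indices or pathway methods. Error control for omics work is often set in an analysis plan or laboratory plan, which is not shown here. That the 0.05 rule reaches these platforms is therefore read from its general wording. This stands, and it is why the size above is conditional on feature-level testing. It does not remove the point, because the published sentence denies adjustment for all tests and makes no exception.

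The second reply is that the article limits its own claims. Significance is declared only for exploratory purposes, and the Discussion says the biomarker results will need validation. This also stands and lowers the severity. Validation still has to start from a chosen list, so the quality of that list matters.

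Third, a small discovery study may prefer sensitivity to error control. The 0.5 SD row of the last table shows that the loss of yield is real. That is a reason to keep reporting the full ranked list, but not to call every unadjusted p below 0.05 significant.

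A reader might go further and infer that most reported hits would probably be false. The article does not support this. Feature count, share changed and effect size are all unstated, and the false share falls to 35% at 10% changed with 0.8 SD, and to 20–31% at 20% changed.

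**Conclusion.** The point holds as a minor one. The no-adjustment rule, as worded, extends to high-dimensional analyses that it suits badly, and nothing else in the article gives those analyses an error rule. If features are tested singly, about 50 per 1,000 unaffected features would be labelled significant. The false share of the list could lie anywhere from about 20% to about 92% over the assumed range (1% to 20% of features changed, 0.5 to 0.8 SD, 27 per arm, independent features). It passes one half only below roughly 6% (0.8 SD) or 10% (0.5 SD) truly changed.

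The feasibility results are not touched. Adherence is estimated without a test, the response comparison does not use omics data, and none of the six progression criteria refers to a biological result. The openly declared lack of adjustment for clinical and patient-reported outcomes is acceptable and is not part of this point.

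**What to change.** Limit the no-adjustment sentence to clinical and patient-reported outcomes. Then add, in substance: where features are tested individually on a high-dimensional platform (gene expression, metabolomics, proteomics, metagenomics), the false discovery rate will be controlled within that platform, for example by Benjamini-Hochberg at a prespecified level such as 10%. The number of features tested, effect sizes, raw p-values and q-values will be reported, and an unadjusted p < 0.05 will not be called significant. The 10% level is a choice for the trial team; what matters is that it is fixed before the data are analysed.

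The cost in work is one or two sentences and a standard software option. With recruitment expected to run to December 2029, this can be settled before the omics data are analysed. The scientific cost is a much shorter list when effects are modest: in the 0.5 SD case above, about 2 hits where 50 features truly differ. Publishing the full ranked list with effect sizes and raw p-values limits that loss, since weaker candidates stay visible without being labelled as findings.

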## Ethics and dissemination

The protocol was approved by the Ethics Committee of the University of Lübeck (2024-182_1) and will be conducted in line with Declaration of Helsinki and ICH-GCP. The study is registered in the German Clinical Trials Register (DRKS00034370). All participants will provide written informed consent as well as broad consent for molecular analyses and may withdraw at any time. Participant data will be handled under EU General Data Protection Regulation and national law. Safety will be overseen by an independent DMC, which will review interim data and may recommend modifications or early termination.

Results will be submitted for publication irrespective of outcome, following CONSORT guidance for randomised trials. Participants will receive a lay summary and may request their individual outcomes. If TRE proves safe, this protocol will inform a larger phase II trial.

## Discussion

FASTINA is the first randomised feasibility study examining 16:8 TRE in MM patients during active therapy. The central question is whether selected MM patients – despite treatment toxicities, steroid-associated metabolic changes, and nutritional challenges – can maintain a daily eating-window intervention without compromising caloric and protein intake. Prior short-term fasting studies in solid malignancies suggest feasibility in some settings [3, 8, 10], but evidence is heterogeneous. In the DIRECT trial, adherence declined over repeated chemotherapy cycles and severe toxicity, and pathological complete response were not significantly improved in the ITT population [11]. Therefore, FASTINA will monitor adherence, dropout, screen-failure reasons, and non-adherence reasons as central feasibility outcomes rather than assuming broad applicability.

Patient safety is paramount and ensured by multiple safeguards, including stringent exclusion criteria, nutritional counselling, DMC oversight, and predefined discontinuation thresholds. We anticipate that TRE can be feasible in well-nourished MM patients, but potential risks include weight loss, inadequate protein intake, sarcopenia, dehydration, electrolyte disturbances, infection-related anorexia, and treatment-related gastrointestinal toxicity. Any signal for toxicity reduction will be interpreted cautiously given the pilot design. A unique consideration in MM is the use of high-dose dexamethasone. Dexamethasone may induce hyperphagia, hyperglycaemia, and circadian metabolic disruption, potentially masking or counteracting fasting-associated metabolic changes [14]. Steroid exposure and biomarker timing will therefore be documented and explored rather than interpreted as pure TRE effects.

While not powered for definitive efficacy, FASTINA’s exploratory outcomes could be hypothesis-generating. Preclinical evidence suggests that tumour cells exposed to nutrient deprivation may demonstrate increased apoptosis when treated with cytotoxic drugs [6, 21]. However, clinical data do not yet support a definitive claim that TRE deepens response or converts MRD status in MM. CR/MRD endpoints are included to estimate effect sizes and variability for a future trial. Our exploratory biomarker analyses – evaluating clonal evolution and metabolomic profiles – may offer mechanistic insights but will require validation.

This study has limitations common to pilot trials [32]. The single-centre design, anticipated slow recruitment, small sample size, and treatment heterogeneity could dilute observable effects and will preclude definitive efficacy conclusions. We enrol both newly diagnosed and relapsed patients, which introduces variability in prognoses and treatments. Additionally, the open-label design could introduce bias from placebo effects or behavioural differences in self-reported outcomes. We equalised contact by providing counselling to both arms, but some bias is inevitably possible. Food diaries are vulnerable to reporting bias, therefore, diary data will be interpreted together with body composition and metabolic biomarkers, while acknowledging that these objective measures are not specific for TRE adherence. Another limitation is the short intervention duration of 3 months – chosen to coincide with typical induction therapy length and to mitigate dropout – which may not be sufficient to influence long-term outcomes like PFS [32]. It will, however, capture initial response. We also acknowledge that our patient population is selected by design – excluding those with frailty, significant weight loss, cachexia or malnutrition – so results may not generalise to all MM patients, especially those who are older or have poor nutritional status [4].

If FASTINA demonstrates feasibility, acceptable safety, and a preliminary response signal, a larger, multicentre phase II trial focusing on efficacy with response rate or PFS as primary endpoint should follow. It could incorporate refinements from FASTINA, such as optimal fasting timing, objective adherence tools, patient education strategies to improve adherence, and robust patient-reported outcome measures. In parallel, the biological samples from FASTINA may yield insights that open new research questions – for instance, if fasting is found to substantially reduce IGF-1 during therapy, one could investigate combining TRE with drugs targeting the IGF-1 pathway [27]. Or if TRE appears to improve T-cell counts or function, it might synergise with immunotherapies like checkpoint inhibitors or CAR-T cells – a hypothesis for future trials [16, 17, 24, 34, 35].

In conclusion, FASTINA represents an initial, safety-focused step in translating metabolic therapy modulation to haematological cancers. A successful outcome – high adherence, preserved nutritional status, no excess toxicity, and a hypothesis-generating efficacy signal – would justify definitive testing. Only larger adequately powered studies can determine whether TRE should become part of supportive MM care. The knowledge gained will contribute to onco-metabolism and may inform future MM management.

## Data Availability

Data are available upon request.

## Abbreviations

AE: Adverse event
AKT: Protein kinase B
ANCOVA: Analysis of covariance
ASCT: Autologous stem cell transplantation
BIA: Bioelectrical impedance analysis
BM: Bone marrow
BMI: Body mass index
CAR T: Chimeric antigen receptor T cell
CI: Confidence interval
CONSORT: Consolidated Standards of Reporting Trials
CR: Complete response
CTCAE: Common Terminology Criteria for Adverse Events
DMC: Data Monitoring Committee
DRKS: German Clinical Trials Register
EORTC QLQ-C30: European Organisation for Research and Treatment of Cancer Quality of Life Questionnaire – Core 30
EU: European Union
FACS: Fluorescence-activated cell sorting
FACIT: Functional Assessment of Chronic Illness Therapy
FACIT-fatigue: Functional Assessment of Chronic Illness Therapy – Fatigue
FACT-G: Functional Assessment of Cancer Therapy – General
GCP: Good Clinical Practice
GDPR: General Data Protection Regulation
HIV: Human immunodeficiency virus
ICH-GCP: International Council for Harmonisation – Good Clinical Practice
IGF-1: Insulin-like growth factor 1
IMiDs: Immunomodulatory drugs
IMWG: International Myeloma Working Group
mABs: Monoclonal antibodies
MRD: Minimal residual disease
mTOR: Mechanistic target of rapamycin
NGS: Next-generation sequencing
NRS-2002: Nutritional Risk Screening 2002
OR: Odds ratio
OS: Overall survival
PFS: Progression-free survival
PI3K: Phosphoinositide 3-kinase
PIs: Proteasome inhibitors
PR: Partial response
QoL: Quality of life
ROS: Reactive oxygen species
SAE: Serious adverse event
sCR: Stringent complete response
SD: Stable disease
SoC: Standard of care
T_0_: Screening
T_1_: End of treatment
T_2_: End of follow-up
TCA: Tricarboxylic acid cycle
TRE: Time-restricted eating
VGPR: Very good partial response
